### **3.4.3 Withdrawal criteria**

Participants may withdraw their consent and discontinue the study treatment at any time. They may withdraw their consent for continued administration of the study medication with or without withdrawing consent from all protocol-specified assessments, follow-up procedures and for the study team to use already collected data. Every effort should be made to encourage participants to return for scheduled visits to undergo study procedures even if they discontinue the study drug. If participants withdraw study participation at any time,

they will be asked if they can participate in one final clinical visit and whether they would participate in a follow-up telephone call seven days later.

## 4.0 INTERVENTION

### 4.1 Study medication

- Group 1 / intervention arm – oral anamorelin HCl 100 mg once daily (administered as tablets in the fasted condition –  $\geq 1$  hour before first meal of the day).
- Group 2 / control arm – placebo once daily (administered as matching placebo tablets regarding appearance, smell and taste, in the fasted condition –  $\geq 1$  hour before first meal of the day).

At baseline, all participants will receive standardised and structured physical activity and diet advice leaflets from the study nurse as part of a multi-modal intervention. All participants will receive the same information delivered in the same way. All other therapies will continue as prescribed by the treating physician(s).

Details of the product information for anamorelin are provided in **Table 4-1**

**Table 4-1 Product Information for anamorelin\***

|                                                                      |                                                                                                                                                                                                                                                                                                                                                  |
|----------------------------------------------------------------------|--------------------------------------------------------------------------------------------------------------------------------------------------------------------------------------------------------------------------------------------------------------------------------------------------------------------------------------------------|
| Approved name                                                 | Anamorelin                                                                                                                                                                                                                                                                                                                                       |
| Manufacturer of drug                                          | Helsinn Healthcare                                                                                                                                                                                                                                                                                                                               |
| Supplier of drug                                              | Helsinn Healthcare                                                                                                                                                                                                                                                                                                                               |
| Approved therapeutic indication, dosage/duration in Australia | Not currently approved.
This study will be conducted through a CTN notification to the Australian Therapeutic Goods Administration (TGA)                                                                                                                                                                                                      |
| Believed mode of action                                       | Selective ghrelin receptor agonist                                                                                                                                                                                                                                                                                                               |
| Dosage regimen                                                | Orally once daily                                                                                                                                                                                                                                                                                                                                |
| Mode of excretion                                             | Most of the drug is excreted in the faeces (92%).                                                                                                                                                                                                                                                                                   |
| Known adverse events                                          | Two phase III clinical trials in patients with advanced lung cancer have demonstrated that anamorelin was well tolerated. The most common drug-related treatment emergent adverse events were diabetes and hyperglycaemia. Grade 1 or 2 nausea was experienced by more patients assigned to anamorelin compared to placebo.         |
| Known contraindications or warnings                           | Special warnings and precautions for use: 
Blood Glucose: Monitoring of blood glucose during treatment with anamorelin, particularly in diabetic patients or in patients with impaired glucose tolerance, is recommended as blood glucose level may increase following anamorelin administration. In patients with |

|  |                                                                                                                                                                                                                                                                                                                                                                                                                                                                                                                                                                                                                                                                                                                                                                                                                                                                                                                                                                                                                                                                                                                                                                                                                                                                                                                                                                                                                                                                                                                                                                                                         |
|--|---------------------------------------------------------------------------------------------------------------------------------------------------------------------------------------------------------------------------------------------------------------------------------------------------------------------------------------------------------------------------------------------------------------------------------------------------------------------------------------------------------------------------------------------------------------------------------------------------------------------------------------------------------------------------------------------------------------------------------------------------------------------------------------------------------------------------------------------------------------------------------------------------------------------------------------------------------------------------------------------------------------------------------------------------------------------------------------------------------------------------------------------------------------------------------------------------------------------------------------------------------------------------------------------------------------------------------------------------------------------------------------------------------------------------------------------------------------------------------------------------------------------------------------------------------------------------------------------------------|
|  | 
pre-existing diabetes mellitus an assessment of the individual benefit-risk balance should be performed.
 
Hepatic impairment: Anamorelin should be used with caution in patients with mild to moderate hepatic impairment as its use in patients with hepatic impairment may be associated with increased exposure to anamorelin.
 
Contra indications:
 
Interactions with CYP3A4: Co-administration of anamorelin with medicinal products that inhibit (e.g ketoconazole, clarithromycin, erythromycin, diltiazem, itraconazole, ritonavir, verapamil) or induce (e.g. rifampicin) CYP3A4 activity may affect anamorelin plasma concentrations. Concomitant administration of anamorelin with strong CYP3A4 inhibitors should be avoided and the concomitant use of anamorelin with moderate CYP3A4 inhibitors should be done with caution. Concomitant administration of anamorelin with strong CYP3A4 inducers should be done with caution.
 
Food effect: Food decreases anamorelin bioavailability and consequently anamorelin should be taken on an empty stomach at least one hour before a meal.
 
Cardiac effects: Anamorelin induced prolongation of PR and QRS intervals at supra-therapeutic doses. Therefore, anamorelin should be used with caution in the case of co-administration of medicinal products that may increase its exposure such as antiarrhythmic medications Class I (fast sodium (NA) channel blockers (e.g. quinidine, disopyramide, procainamide, lidocaine, phenytoin, flecainide, propafenone).
 |
|--|---------------------------------------------------------------------------------------------------------------------------------------------------------------------------------------------------------------------------------------------------------------------------------------------------------------------------------------------------------------------------------------------------------------------------------------------------------------------------------------------------------------------------------------------------------------------------------------------------------------------------------------------------------------------------------------------------------------------------------------------------------------------------------------------------------------------------------------------------------------------------------------------------------------------------------------------------------------------------------------------------------------------------------------------------------------------------------------------------------------------------------------------------------------------------------------------------------------------------------------------------------------------------------------------------------------------------------------------------------------------------------------------------------------------------------------------------------------------------------------------------------------------------------------------------------------------------------------------------------|

*\*Further information is in the investigator brochure.*

## 4.2 Dosing schedule

The first day of dosing will be Day 1. The intervention will be delivered as one blinded tablet: one anamorelin HCl 100 mg tablet or one matching placebo tablet. Tablets of study drug are to be taken orally, once daily by the participant in mornings while fasting at least 1 hour before the first meal of the day. Water is permitted prior to and with study drug. Participants will take the first dose of intervention on Day 1, which is the day after receipt of the medication. If a fasting state is not possible on Day 1, participants will start study drug on the next possible day and daily thereafter until Week 12 or up to week 24, if a participant opts in for blinded continuation in the extension phase. If participants have missed any doses, irrespective of the number of doses missed, they will be instructed to not catch up the missed doses if the missed dose was more than 8 hours earlier, but to continue taking on the next day of treatment. Participants will be supplied with study drug within business days after randomisation (i.e. up to one day prior to starting Cycle 2 of chemotherapy) and at Week 18.

### 4.3 Method of assigning participants to treatment groups

At each site, people referred to the study will be sequentially allocated a unique identification (ID) number. This ID number will be used for all subsequent study documentation for that participant.

Treatment for each participant will be allocated in a 1:1 ratio. Block randomisation will occur in each stratum at each site in randomly assigned blocks of 4 or 8 and will ensure even allocation to each code. Central randomisation will be stratified by limited versus extensive disease and by baseline score of the 5-item Anorexia Symptom Scale Domain from the 12-item FACCT A/CS ( $\leq 10$  vs  $>10$ ). The 5-item from the FACCT A/CS are as follows: *F1. I have a good appetite; F6. My interest in food drops as soon as I try to eat; F7. I have difficulty eating rich or "heavy" foods; F10. When I eat, I seem to get full quickly; F4. Most food tastes unpleasant to me.*

On notification of a participant, the delegated pharmacist at a third party pharmacy will email the ITCC Central Randomisation Service ([contact]) providing the required registration details and receive the treatment allocation via reply email. This allocation will be printed or saved electronically into the pharmacy records. The participant ID, allocation code, dates of request, preparation, and dispensing will be recorded in a log maintained by the pharmacist and supplied to the central registry on each randomisation.

Participant randomisation will be registered with the IMPACCT Trials Coordination Centre (ITCC). In summary, the procedure outlines that, on randomisation of a participant, the third party pharmacy is to email a notification to the ITCC. This notice will be monitored alongside the participant eligibility as entered onto the electronic Case Report Form (eCRF) from the Eligibility data collection worksheet.

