## 5.0 OUTCOMES AND MEASURES

### 5.1 Primary Outcome

#### 5.1.1 Feasibility

Progression criteria will be assessed using an indicative traffic light system (green, orange red) whereby green (go) suggests that the criteria have been met and the trial should proceed, orange (amend) indicates that some changes should be made to the larger trial and red (stop) indicates that a larger trial should not proceed. Feasibility will be assessed by evaluating:

1. **Recruitment rate**, defined as an average of one participant per site (six sites) every six weeks – plan to recruit 50 participants.
2. **Proportion of participants with complete primary endpoint data** – >70% (green), 60-70% (orange), <60% (red).
3. **Participant adherence to investigational medication** – >70% (green), 60-70% (orange), <60% (red).
4. **Participant adherence to physical activity advice**, as measured by the Short Questionnaire to Assess Health Enhancing Physical Activity (SQUASH), completed at every visit (whereby increase in physical activity will be reviewed over the study period) – >40% (green), 30-40% (orange), <30% (red).
5. **Participant adherence to dietary advice**, as measured by the food diary kept for three days prior to visits (whereby increase in macronutrients intake will be reviewed over the study period) – >40% (green), 30-40% (orange), <30% (red).

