## 10.0 STATISTICS

### 10.1 Power and sample size

A total of 50 participants with small cell lung cancer will be randomised 1:1 to anamorelin HCl 100 mg or placebo in order to have data at 12 weeks on 40 participants (approximately 20 in each treatment arm). Since this is a feasibility study, it is not required to calculate a fully justified sample size for establishing the efficacy of the intervention. It has been suggested, however, that in feasibility studies, a sample size between 24 and 50 is acceptable. The findings from this study will be used to inform the calculation of a sample size for a future larger scale phase III trial.

Participants discontinued after randomisation will not be replaced.

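### Blocks of 4 or 8 nested in site, disease extent and appetite score give 24 cells for 50 participants, so section 4.3 cannot ensure even allocation or reliable balance on the stratification factors

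*Supplement*

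**What the plan says.** Section 4.3 sets the ratio: "Treatment for each participant will be allocated in a 1:1 ratio". It then runs the blocks "in each stratum at each site in randomly assigned blocks of 4 or 8 and will ensure even allocation to each code". The next sentence names the stratifiers: "Central randomisation will be stratified by limited versus extensive disease and by baseline score of the 5-item Anorexia Symptom Scale Domain", with the score cut at 10 or below against above 10. Site is not in that list.

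Section 8.6 makes the prescription the randomisation request. Section 8.7 lists the stratification details it must carry as disease extent and FAACT score, again without site.

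On numbers, the recruitment criterion in section 5.1.1 is "an average of one participant per site (six sites) every six weeks". Section 10.1 states "A total of 50 participants with small cell lung cancer will be randomised 1:1 to anamorelin HCl 100 mg or placebo" and gives the aim as "in order to have data at 12 weeks on 40 participants (approximately 20 in each treatment arm"). No overall balance constraint, minimisation or cap on imbalance is described.

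In section 10.3 the only named between-arm tests are a t-test or a Wilcoxon test on change from baseline. No adjustment for stage or baseline score is mentioned.

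**The concern.** A permuted block guarantees balance only when it is complete. Splitting a small trial into many cells leaves most blocks unfinished. Each unfinished block can leave a surplus in one arm, and these surpluses add up across cells because nothing ties them together. Stratifying on more factors can then give less balance on the ones that matter.

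Two things could be at stake: the overall arm sizes, and the balance between arms on disease extent and baseline appetite score. The second matters more. The protocol chose these two factors to stratify on, and the comparison rests on about 20 people per arm. It also feeds the desirability judgement in section 5.1.2, which looks for a sufficient efficacy signal. A chance difference in stage could blur or mimic that signal, and an unadjusted test would not correct for it.

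**Working it through.** The protocol gives no imbalance figure to reproduce; it only asserts even allocation.

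**Inputs from the protocol.** 50 randomised 1:1 (10.1); blocks of 4 or 8 in each stratum at each site, with two binary stratifiers (4.3); six sites (5.1.1).

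**Assumptions, because the protocol is silent.** The mix of block sizes, and how participants spread over sites, stage and score.

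**1. Cells.** 6 × 2 × 2 = 24 cells; 50/24 = 2.08 participants per cell.

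**2. How many cells fill a block.** With equally likely cells, a cell's count is binomial (50, 1/24). The chance of 3 or fewer is 0.85, of which (23/24)^50 = 0.12 is an empty cell. So about 85% of cells never complete a block of 4, and fewer still complete a block of 8.

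**3. Imbalance in an unfinished block.** With n participants in a block of size b, the number in one arm is hypergeometric, and the arm difference has variance n(b − n)/(b − 1). For n = 2, both go to the same arm with probability (b/2 − 1)/(b − 1), which is 1/3 for b = 4 and 3/7 for b = 8.

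**4. Hand check.** Take 22 cells of two and 2 cells of three (50 people), with an equal mix of block sizes.
- Variance per cell of two: (4/3 + 12/7)/2 = 1.524.
- Variance per cell of three: (1 + 15/7)/2 = 1.571.
- Total: 22 × 1.524 + 2 × 1.571 = 36.7, so the SD of the arm difference is 6.1.
- A 28:22 or worse split is a difference of 6 or more. The difference moves in steps of 2, so the normal approximation is P(|Z| > 5/6.06) = 0.41. The exact convolution also gives 0.41.

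**5. Random cell counts.** P(28:22 or worse, either direction), exact within cells and averaged over 1,500 multinomial draws (the fixed-count row is exact):

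| Spread of the 50 | All blocks of 4 | Equal mix | All blocks of 8 |
|---|---|---|---|
| 24 equal cells | 0.273 | 0.345 | 0.400 |
| 24 cells, stage 33/67 | 0.261 | 0.333 | 0.388 |
| 24 cells, stage and score both 30/70 | 0.244 | 0.315 | 0.364 |
| 24 cells, uneven sites (35/25/15/10/10/5%), stage 33/67 | 0.234 | 0.300 | 0.350 |
| 22 cells of two, 2 of three | 0.369 | 0.407 | 0.440 |
| Site dropped: 4 cells, stage 33/67 | 0.003 | 0.023 | 0.032 |

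Simple randomisation without blocks gives 0.48. In the equal-cell, equal-mix case the SD of the arm difference is 5.3 and an exact 25:25 split occurs with probability 0.15.

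**6. Cost of the split itself.** (1/28 + 1/22)/(2/25) = 0.0812/0.0800 = 1.015, or 1.5% more variance. At 30:20, (1/30 + 1/20)/(2/25) = 0.0833/0.0800 = 1.042.

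**7. Balance on stage.** Simulation with six equal sites, 65% extensive disease, half with a low score and an equal block mix:
- The arms differ by 10 percentage points or more in extensive disease in about 34% of trials, against about 3% with the same blocks in four cells.
- Among limited-stage participants, the arms differ by 4 or more people in about 30% of trials, against 2% to 3% without site and 40% under simple randomisation.

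**The case against.** Several points on the other side have force.

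- **Site may not be a stratifier.** The sentence naming the factors and the prescription content in section 8.7 both omit site. If the list is run centrally on the two named factors, the 28:22 risk is about 2% and little is left of the concern. This stands as an ambiguity. But the blocking sentence does nest blocks in site, and a list built from it would have 24 cells. Either way section 4.3 needs an edit.
- **The overall split does little harm.** A reader might infer that the target of about 20 evaluable per arm, or the trial's power, is undermined. The documents do not support that. Section 10.1 says approximately 20, makes no power claim, and the variance cost is 1.5% at 28:22. With 40 evaluable and an assumed standardised effect of 0.8, power is 69.3% at 20:20 and 68.9% at 22:18.
- **Chance imbalance is not bias.** Randomisation stays valid, the feasibility thresholds have no between-arm criterion, and section 10.3 calls the arm comparisons exploratory. All true. It limits the weight of the point but does not make the stated assurance correct.
- **The blocks still do something.** They lower P(28:22 or worse) from 48% to about one third. Ending on an incomplete block is also a poor yardstick: with the same blocks in four cells, about 83% of cells still end that way.
- **Blocking within site is a recognised choice**, made to protect against differences between sites. With about two people per cell, it gives little of that protection here.

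**Conclusion.** The point holds, at moderate weight. As written, section 4.3 produces 24 cells of about two people and does not deliver the even allocation it promises. The chance of 28:22 or worse is about 23% to 44%. One in three is the figure for an equal mix of block sizes and should not be quoted without that condition. Even the lowest value is inconsistent with an assurance of even allocation.

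The harm to put forward is lost balance on disease extent and score, with no adjustment named in the analysis, rather than lost precision from unequal arms. The one-third figure for a 10-point gap in extensive disease rests on assumed prevalences (65% extensive, half with a low score), equal sites and an equal block mix. All these results depend on reading the blocking as nested in site.

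**What to change.** Reconcile section 4.3 with section 8.7 by stating that site is not a stratification factor. Randomise centrally within the four disease-extent by 5-item-score cells using small permuted blocks, for example blocks of 4. That brings P(28:22 or worse) to about 0.3%. Remove the assurance of even allocation or replace it with what the scheme provides.

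The cost is a new randomisation list and a short edit to section 4.3. Allocation already comes from a central service, and dispensing from one third-party pharmacy in blinded packaging, so site blocking is not needed for supply. The downside is that balance within each site is no longer targeted, though cells of about two people barely achieve it now. Minimisation on the two factors is an alternative, but it needs a running algorithm at a service that now works by email, so it costs more than a new list. Blocks of 2 would be more predictable than blocks of 4.
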